## Introduction

1

Sepsis and septic shock are the most severe forms of infection.^[1]^ In addition to elderly patients, sepsis affects most often young children, as well as term and, in particular, preterm neonates, causing about 8% of admissions to pediatric intensive care units (PICUs) in high-income countries.^[2–8]^ Worldwide, an estimated 1.2 million cases of childhood sepsis occur each year.^[3,8]^ Therefore, with 2202 cases per 100,000 live births, the main burden is on neonates. Moreover, beyond the newborn period, children with chronic diseases have an increased risk of developing sepsis including hematologic and oncologic diseases, metabolic, neurologic, cardiac, and renal diseases as well as solid organ transplanted children.^[9]^ Both in adults and children, the triad of early diagnosis, rapid initiation of a causal therapy (consisting of a broad anti-infective therapy with prompt source control), and immediate hemodynamic stabilization is pivotal for patient survival. While the initial antimicrobial treatment regimen has to be empirical in most cases, the identification of the causative pathogen is crucial for patient disease course. This is due to the fact that an early de-escalation of the antibiotic regime, defined as the change from a broad-spectrum antibiotic agent to one with a narrower spectrum, is associated with lower mortality in patients with sepsis or septic shock.^[10]^ However, it is only safe to de-escalate within the first 72 hours once culture-results are available. But although these culture-based methods still represent the gold standard for pathogen identification today, they are associated with considerable limitations.^[11,12]^ First of all, culture-based methods are associated with a relevant time delay. Depending on the amount of microbes as well as the particular species in the original sample, it takes up to 5 to 7 days until the final results, including resistance patterns, are available.^[13]^ Secondly, they are often false-negatives. Even in highly selected patients suffering from proven endocarditis, using 1 set of blood cultures (1 aerobic and 1 anaerobic bottle, 8–10 mL each), bacteremia or fungemia can be detected with a sensitivity of around 70%.^[14]^ Sensitivity increases to 80% to 90% with the second set of blood cultures and over 98% can be achieved with the third.^[14]^ In less preselected patients with septic shock due to various infection foci, positive rates of blood cultures were only at 11%.^[15]^ In small children, positivity rates are even lower as such volumes (6 × 10 mL = 60 mL) cannot be collected in young children (e.g., a term newborn with a bodyweight of around 3 kg has a blood volume of only about 240 mL) without resulting in severe hemodynamic instability. As a result, blood-cultures of pediatric patients with sepsis remain negative in >90% of cases,^[16]^ making a reliable de-escalation of the antibiotic treatment regime more difficult. Thirdly, culture-based methods for pathogen detection have a high risk of contamination, whereby the results become false positive. As a result, patients suffering from sepsis or septic shock are frequently over-treated with antimicrobial drugs which, in turn, favors the selection of multi-drug resistant pathogens and increases the risks of drug-related toxicities. The latter are particularly significant in preterm and term neonates, in which detoxification-systems have not yet been fully developed.^[17]^

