## Question and justification of the project (rationale)

2

This prospective, observational, non-interventional, multicenter study on the diagnostic use of NGS in neonates (d0–d28, n = 50), infants (d29 to <1 yr, n = 50), and toddlers (1 yr to <5 yrs, n = 50) suffering from severe sepsis or septic shock is designed to provide evidence for the effectiveness of an NGS-based approach in the quantitative measurement of pathogen load in blood samples from patients in the above-mentioned age groups. It is a clinical trial on a new technique designed to overcome a long-lasting problem on pediatric intensive care units and to replace the previous culture-based gold standard of microbial diagnosis in septic children. The study protocol of the Next GeneSiPS-Trial is very close to that of the Next GeneSiS-Trial, which investigated the performance of an NGS-based approach using the SIQ-Score in 500 adult patients with sepsis and septic shock.^[21,22]^ After a successful interim analysis of the Next GeneSiS-Trial, the Next GeneSiPS-Trial now seeks to extent the findings to newborns, infants, and toddlers.

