## Objectives

3

First of all, the Next GeneSiPS-Trial aims to evaluate the performance of a NGS-based approach for the detection of the relevant infecting organisms in newborns, infants, and toddlers with suspected or proven severe sepsis or septic shock by the use of the quantitative sepsis indicating quantifier (SIQ) score in comparison to standard (culture-based) microbiological diagnostics. Second, we plan to assess the clinical value of NGS-based diagnostics asking a panel of 3 independent clinical experts to retrospectively identify potential changes in patient management strategies based on the presented NGS results.

Moreover, secondary objectives will be assessed:

Evaluation of antimicrobial resistance patterns and virulence factors.Evaluation of processing times for NGS-based measurements.Diagnostic or prognostic value of host nucleosome positioning patterns derived from plasmatic cell-free DNA in patients with suspected or proven severe sepsis or septic shock.^[23,24]^Diagnostic value of host expression profiles including RNA-derived biomarkers in patients with suspected or proven severe sepsis or septic shock.Examination of the metabolome in plasma and urine to identify risk profiles.

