### Microbiological diagnostics

5.10

Parallel to the collection of the basic data, at sepsis onset, 72 hours after sepsis onset and, if indicated by the treating physician, at a maximum of one further time within the first 3 days after sepsis onset, samples for NGS-based diagnosis with subsequent calculation of the SIQ score by the Fraunhofer IGB will be collected. Routine microbiological findings from other sample materials (e.g., surgical swabs, drainage secretions, tracheal secretions, tissue samples, etc) are included in the evaluation, provided that they have been preserved in a time window of 72 hours before or after plasma samples are obtained for NGS-based diagnostics.

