### Statistical methods

5.16

As the Next GeneSiPS-Trial has to be understood as an extension of the Next GeneSiS-Trial, statics will be carried out as previously published.^[22]^ In brief, case by case NGS results will be compared with those obtained using standard-of-care microbiological testing. The McNemar test and Cohen *κ* statistics are used to check the agreement and concordance.^[40,41]^ All percentages and confidence intervals (Cis) are calculated using exact methods and rounded accordingly. The clinical value of NGS-based diagnostics is determined as follows: 3 independent experts (not associated with the study site) compare the results obtained using NGS-based diagnostics with those of routine microbiological diagnostics and evaluate the findings using a special questionnaire with regard to their relevance for the anti-infective therapy strategy. The evaluation of the questionnaire is carried out according to the majority rule. Further subgroup analyses will focus on patients in whom the anti-infective therapy did not work sufficiently, that is, in whom organ dysfunction did not improve or who have died (Chi-squared test for categorical data and further methods of variance analysis for continuous data). The statistical evaluation is carried out by means of SAS (SAS Institute, Cary, NC). Detailed descriptive statistics will be provided for all data collected. The chi-square test will be used for evaluating categorical variables and *t* tests will be used for evaluating continuous data univariably. Appropriate regression methods will be used for multivariable analyses. A *P*-value of <.05 is assumed to be statistically significant. However, given that the Next GeneSiPS-Trial is a not statistically powered study of exploratory nature, these values are only of descriptive value.

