## Discussion

6

In the 2016 International Guidelines for Management of Sepsis and Septic Shock (of adult patients), the Surviving Sepsis Campaign (SSC) states that “appropriate routine microbiologic cultures always include at least two sets of blood cultures (aerobic and anaerobic).” The reason for this is the fact that the first pair of blood cultures achieves only a sensitivity of about 70% regarding the identification of the causative pathogens of bloodstream infections.^[14,15]^ The second pair accomplishes a sensitivity of 80% to 90%, resulting in over 98% with the third pair.^[14,15]^ If one considers all septic patients (and not only those with bloodstream infections), the causative pathogen is only successfully identified in one-third of cases.^[45–47]^ Underlying reasons might be technical shortfalls in blood culture acquisition, locally limited foci, fastidious organisms, or very low rates of viable microorganisms in blood stream further reduced by the beginning of antibiotic treatment before sample acquisition.^[22,48]^ In children, these limitations are of particular importance as blood volumes are small. Therefore, the SSC “international guidelines for the management of septic shock and sepsis-associated organ dysfunction in children” recommends “obtaining blood cultures before initiating antimicrobial therapy” but only “in situations where this does not substantially delay antimicrobial administration,”^[8]^ as a delayed onset of anti-infective treatment increases organ dysfunction in pediatric sepsis.^[48,49]^ In this context, the SSC mentions the potential benefit of new molecular technologies including the restriction, that currently used sequencing systems are limited to a predefined set of detectable pathogens.^[8,50]^ A prominent example is the direct detection of the (deoxy)ribonucleic acid (DNA/RNA) sequences of pathogens by means of polymerase chain reaction (PCR). It is a highly sensitive and specific, culture-independent method for the targeted detection of a specific pathogen.^[28–30,51,52]^ In particular, it enables the detection of pathogens that are difficult to cultivate, such as atypical pneumonia pathogens, viruses, or fungi.^[28,51]^ A pathogen can potentially be detected even if it has already been killed or significantly reduced in number by the first administration of antimicrobial therapy.^[53,54]^ However, in this context, it is necessary to distinguish between pathogen-specific and so-called broad-spectrum or universal PCR methods. In the first case, the DNA of specific pathogens is identified by the use of specific primers, while in the second case, primers are used which bind to conserved sections of the genome of bacteria or fungi. These so-called eubacterial or pan-fungal PCRs allow a broader search approach, but are significantly less sensitive. Moreover, it is often only possible to identify the pathogen family rather than the specific species.

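### McNemar's test compares only positivity rates, and kappa falls mechanically if NGS is positive far more often than the comparator; neither should be the headline measure of diagnostic performance

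*Protocol article*

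**What the plan says.** The first objective (section 3, Objectives) is diagnostic: the trial "aims to evaluate the performance of a NGS-based approach for the detection of the relevant infecting organisms" in comparison with standard, culture-based diagnostics. The rationale in section 2 goes further and describes a technique intended "to replace the previous culture-based gold standard of microbial diagnosis in septic children".

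Section 5.16 (Statistical methods) says in summary that "case by case NGS results will be compared with those obtained using standard-of-care microbiological testing". McNemar's test and Cohen's kappa are the two methods it names for this, and these "statistics are used to check the agreement and concordance". The section also promises percentages with exact confidence intervals, without saying which percentages, and refers to the published adult trial for the rest. It calls P-values descriptive only.

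Three further statements bear on how the two statistics would behave:

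- The Introduction says that "blood-cultures of pediatric patients with sepsis remain negative in >90% of cases". It also describes culture as often falsely negative and prone to contamination, and NGS as the more sensitive tool.
- The comparator is wider than blood culture. Section 5.10 says that "Routine microbiological findings from other sample materials" are included if obtained within 72 hours before or after the plasma sample.
- The expert panel (sections 5.4 and 5.16) judges whether NGS results might have changed treatment. It is not described as deciding which organism was the true cause.

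**The concern.** McNemar's test is given a job it does not do. Its null hypothesis is that the two methods have equal positivity rates. It uses only the difference between the two kinds of discordant pair, so it measures neither agreement nor accuracy. A small P-value says that one method is positive more often, and a large one does not mean that the two agree.

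Kappa does measure agreement, but its attainable maximum depends on how far apart the two positivity rates are. The protocol expects NGS to detect more than culture. If it does, kappa falls even when NGS misses nothing that the comparator found.

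A reader could therefore take a significant McNemar result as proof of better detection, or a low kappa as failure of the assay, and neither follows. Both statistics also treat an NGS-only positive in the same way whether it is a real infection that culture missed or a contaminant. For a technique meant to replace culture, that is the central question.

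**Working it through.** The article states no expected kappa, power or NGS positivity, so there is no figure to reproduce. The check is how the two statistics behave at the planned size.

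**Inputs**

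- N = 150 septic children, 50 per age group (section 5.11).
- Comparator positivity of 10%, the upper limit implied by the Introduction's figure for paediatric blood cultures: 15 positive, 135 negative.
- Comparator positivity of 33% as an assumed higher value, because other specimens count. The Discussion says of septic patients in general that "the causative pathogen is only successfully identified in one-third of cases".
- NGS positivity is not given. Assumed range: 30% to 70%.

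**Step 1: McNemar's test.** The exact test is a two-sided binomial test with probability 0.5 on the discordant pairs.

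| Both + | NGS only | Comparator only | Both − | McNemar P | Kappa |
|---|---|---|---|---|---|
| 15 | 0 | 0 | 135 | 1 | 1.00 |
| 0 | 15 | 15 | 120 | 1 | −0.11 |
| 15 | 90 | 0 | 45 | 1.6 × 10⁻²⁷ | 0.09 |
| 5 | 100 | 10 | 35 | 8.0 × 10⁻²⁰ | −0.11 |

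Rows 1 and 2 are perfect agreement and disagreement on every positive, and the P-value is the same. In rows 3 and 4 NGS is positive in 105 children each time. It finds all 15 comparator positives in one and only 5 of 15 in the other, yet both P-values are extremely small.

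A test with no information behaves in the same way. If NGS were positive at random in 50% of children, the expected discordant counts are 135 × 0.5 = 67.5 and 15 × 0.5 = 7.5. Rounded to 68 and 8, the exact P is about 6 × 10⁻¹³.

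**Step 2: ceiling on kappa.** Let pc be comparator positivity, pn NGS positivity, pn ≥ pc, with every comparator positive also found by NGS:

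- observed agreement Po = pc + (1 − pn)
- chance agreement Pe = pc·pn + (1 − pc)(1 − pn)
- maximum kappa = (Po − Pe) / (1 − Pe)

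| pc | pn | Po | Pe | Maximum kappa |
|---|---|---|---|---|
| 10% | 10% | 1.00 | 0.82 | 1.00 |
| 10% | 30% | 0.80 | 0.66 | 0.14 / 0.34 = 0.41 |
| 10% | 50% | 0.60 | 0.50 | 0.10 / 0.50 = 0.20 |
| 10% | 70% | 0.40 | 0.34 | 0.06 / 0.66 = 0.09 |
| 33% | 50% | 0.83 | 0.50 | 0.33 / 0.50 = 0.66 |
| 33% | 70% | 0.63 | 0.432 | 0.198 / 0.568 = 0.35 |

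The first row shows that the ceiling comes from unequal rates, not from low positivity in itself.

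**Step 3: true or false extras.** At 10% against 30%, the best-case table is 15, 30, 0, 105, with kappa 0.41 and P = 1.9 × 10⁻⁹. These counts are the same whether the 30 NGS-only positives are real infections or contaminants, so neither statistic can respond to the difference.

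**Step 4: percent agreement.** Positive percent agreement is both-positive divided by comparator-positive. Negative percent agreement is both-negative divided by comparator-negative. With Clopper-Pearson 95% intervals:

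- Row 3 of Step 1: positive 15/15 = 100% (78% to 100%), negative 45/135 = 33% (26% to 42%).
- Row 4: positive 5/15 = 33%, negative 35/135 = 26%. The loss of comparator positives is now visible.
- Other positive agreement results: 12/15 = 80% (52% to 96%). In one age group with 5 comparator positives, 5/5 = 100% (48% to 100%).

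Percent agreement separates the two kinds of discordance. It does not by itself show which NGS-only positives are true.

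**The case against.** The strongest reply is that section 5.16 is an abridged summary of an exploratory study. It defers to the adult trial's published methods, plans a case-by-case comparison and exact percentages, and treats P-values as descriptive. McNemar's test and kappa are also used together: a random test would have an expected kappa of zero, so the pair would not present it as agreeing with the comparator. The SIQ score is itself built against control samples to separate pathogens from contaminants.

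Much of this stands, and it limits the point. Three stronger readings that a reader might infer are not supported:

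- **That kappa must be near zero because over 90% of cultures are negative.** At equal positivity rates its maximum is 1.00. At 10% comparator positivity it falls to about 0.09 only when NGS is positive in about 70%, and the article gives no NGS rate. The figure above 90% also concerns blood cultures alone, whereas the comparator includes other specimens.
- **That the plan cannot answer its first objective.** Percentages with exact intervals are planned, and the full protocol or analysis plan may define them as accuracy or agreement measures.
- **That repeat samples will be pooled as if independent, or that different species will count as agreement.** Section 5.10 allows a sample at onset, one at 72 hours and, if the physician sees an indication, another "at a maximum of one further time within the first 3 days after sepsis onset". Nothing says these will be pooled, and a case-by-case comparison points the other way. The unit and the species matching are details that an article may leave to the full plan.

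What the reply does not remove is the statement itself. The article assigns McNemar's test to agreement, which it does not measure. Calling P-values descriptive does not help, because a descriptive statistic must still describe the quantity of interest, and kappa can mislead without any P-value.

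**Conclusion.** The point holds as a misapplied method for the first objective, not as a missing detail. That McNemar's test measures neither agreement nor accuracy needs no assumption. The size of the kappa problem depends on NGS positivity, which is assumed here: the ceiling runs from 0.41 down to 0.09 at 10% comparator positivity (NGS 30% to 70%), and is 0.66 or 0.35 at an assumed 33% (NGS 50% or 70%). It matters to the extent that NGS is positive more often than the comparator, which is the result the protocol expects. Neither statistic distinguishes true from false additional detections, and the panel's stated task, treatment change, does not fill that gap. The change is worth making before results are seen, but the point does not invalidate the study.

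**What to change.** In section 5.16:

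1. Name positive and negative percent agreement with standard-of-care microbiology, with exact 95% confidence intervals, as the headline performance measures. Report them overall and for each age group, using one pair per child from the onset sample.
2. Describe McNemar's test only as a comparison of the two positivity rates.
3. Report kappa only beside the maximum attainable at the observed positivity rates.
4. Optionally, add one item to the existing panel questionnaire that classifies each NGS-only positive as causative, possible or contaminant. This is the step that addresses whether the extra detections are real.

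Items 1 to 3 change wording and reporting on data already planned. The costs are that the headline intervals will look wide, above all within age groups, and that agreement is still measured against a reference the protocol itself calls imperfect. Item 4 changes the questionnaire and adds a little work for the panel.

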### Data monitoring

5.17

Each participating site is assigned to a clinical monitor of the Coordination Centre for Clinical Trials (KKS), Heidelberg University (Heidelberg, Germany). By keeping close contact with the respective site investigators (e-mail, telephone, video call apps), the monitor will ensure that the trial is being conducted according to the protocol and regulatory requirements. If necessary, the clinical monitor will visit the participating sites to review the entries into the eCRFs on the basis of source documents.

### Harms

5.18

Due to the non-interventional character of the Next GeneSiPS-Trial, study-related adverse events (AE) are restricted to the complications of study-related blood draws of a maximum of 3 draws of 2.7 mL within 72 hours. Blood will only be taken during routine blood draws. Therefore, it is not possible to cause additional harm by study-related vascular punctures. For the same reason, no serious AEs (SAE) (death, a life-threatening state, a prolongation of existing hospitalization, a persistent or significant disability or incapacity due to study participation) are expected. Nevertheless, possible (S)AEs can be recorded in the eCRF.

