**Methods::**

The Next GeneSiPS-Trial is a prospective, observational, non-interventional, multicenter study used to assess the diagnostic performance of an NGS-based approach for the identification of causative pathogens in (preterm and term) neonates (d1–d28, n = 50), infants (d29 to <1 yr, n = 50), and toddlers (1 yr to <5 yr, n = 50) with suspected or proven severe sepsis or septic shock (according to the pediatric sepsis definition) by the use of the quantitative sepsis indicating quantifier (SIQ) score in comparison to standard of care (culture-based) microbiological diagnostics. Potential changes in anti-infective treatment regimens based on these NGS results will be estimated retrospectively by a panel of 3 independent clinical specialists.

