
In order to overcome these challenges, we recently introduced the concept of an unbiased sequence analyses of circulating cell-free deoxyribonucleic acid (cfDNA) by next-generation sequencing (NGS) for sepsis diagnostics.^[18–20]^ Using a quantitative score (sepsis indicating quantifier [SIQ] score), this NGS-based approach enables clinicians on the one hand to identify the relevant infecting organisms and on the other to differentiate the sepsis-causing pathogen from potential microbial contaminants (e.g., coagulase-negative staphylococci). Therefore, this method has proven to be superior to state-of-the-art molecular approaches for the diagnosis of infecting organisms (such as polymerase chain reaction [PCR]-based methods for pathogen identification) in specimens of septic patients. In contrast to these conventional PCR-based diagnostic procedures, NGS is an open approach and therefore not limited to the identification of a predefined list of probable species.

As newborns, infants, and toddlers are particularly susceptible to the toxic side effects of anti-infective drugs due to immature detoxification systems, they could exceptionally benefit from this quicker, more sensitive diagnostic tool, needing only 1 mL of patient blood.

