### Next-generation sequencing (NGS)

5.6

The NGS-based diagnostics in the plasma samples of the study patients is carried out as follows (subject to any further technical developments).^[20]^ After the aseptic removal of 2.7 mL EDTA blood, EDTA plasma is obtained immediately by centrifugation for 10 minutes at 2500 × *g*. The plasma is then pipetted into 0.5 mL Eppendorf or 1.5 mL DNA LoBind tubes. Then, 80 μL is pipetted into a separate 0.5 mL Eppendorf tube in order to later determine the concentration of the reactive metabolite methylglyoxal (MG) from this.^[31]^ The Eppendorf tubes are then stored at –80 °C until further processing. Sample processing should be completed no later than 2 hours after the blood sample has been taken. The sample is transported for further processing to the Fraunhofer Institute for Interfacial Engineering and Biotechnology (Fraunhofer IGB, [name]) on dry ice. Here, plasma will be centrifuged again for 10 minutes at 16,000 × *g* and 4 °C and nucleic acids will be isolated using the QIAsymphony DSP Circulating DNA Kit (Qiagen, Hilden, Germany). The isolated nucleic acids (=freely circulating DNA [cfDNA]) are then quantified using the Qubit dsDNA HS Assay Kit (Life Technologies, Carlsbad, CA). In addition, quality control is carried out using the HS NGS Fragment Analysis Kit using a Fragment Analyzer or FEMTO Pulse (Advanced Analytical Technologies Inc., Heidelberg, Germany). The so-called NGS libraries are made from 0.5 to 1 ng cfDNA using the Nextera XT Library Preparation Kit (Illumina, San Diego, CA) or NEXTflex Cell Free DNA-Seq Kit (Bioo Scientific, Austin, TX) and then sequenced on a HiSeq2500 (Illumina, San Diego, CA). In the next step, human cfDNA is identified using NextGenMap. Reads mapping to the human reference genome (hg19, minimum identity between read and reference genome of 80%) and reads with low complexity (consecutive stretches of di- and trinucleotides along the whole read sequence) are excluded from further analysis.^[32]^ Finally, reads are assigned to systematic classification using the RefSeq database (release version 68; comprising 35,749 bacterial and 4340 viral genomes complemented by 12 selected fungal genomes) using the Kraken Taxonomic Sequence Classification System (Center for Computational Biology, Johns Hopkins University, Baltimore, MD).^[33,34]^ To quantify the respective reads, read counts are normalized to the corresponding library size. Of note, *Xanthomonas* species are excluded from further analyzes as they are well-known contaminants.^[35]^

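### One NGS draw volume of 2.7 mL, up to three times in 72 hours, is stated for every child, including preterm neonates with no weight floor, although the article says the method needs 1 mL

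*Protocol article*

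**What the plan says.** Section 5.6 opens the laboratory procedure with one blood volume: "After the aseptic removal of 2.7 mL EDTA blood". Section 5.18 repeats that volume as an upper bound, the "complications of study-related blood draws of a maximum of 3 draws of 2.7 mL within 72 hours". Neither place qualifies it by age or weight.

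The schedule is in section 5.10: a sample at onset, one at 72 hours, and another "if indicated by the treating physician, at a maximum of one further time within the first 3 days after sepsis onset". Table 5 puts the 72-hour NGS sample in brackets.

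The population includes the smallest patients. The abstract sets the aim as "identification of causative pathogens in (preterm and term) neonates", and section 6.1 again names preterm neonates. Table 1 (section 5.2) restricts age but has no minimum weight or gestational age.

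The Introduction says that these children could benefit from a tool "needing only 1 mL of patient blood". It also gives a term newborn of about 3 kg a blood volume of about 240 mL.

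On risk, section 5.18 reasons that study blood is taken only at routine draws, so no puncture harm is added, and for that same reason expects no serious events. Section 5.23 describes the blood loss as low and attaches no weight to that description.

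**The concern.** A fixed volume takes a share of blood that rises as weight falls. The article recognises this for blood cultures: the Introduction explains why adult culture volumes cannot be taken from a newborn, and the example in section 5.5 lets the culture volume vary from 0.5 to 10 mL with the blood available. The stated study draw has no such adjustment, although the children enrolled have severe sepsis or septic shock.

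The Harms reasoning covers the needle and leaves out the volume. Using a routine draw removes the extra puncture, but the extra millilitres are still taken.

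At stake is avoidable blood loss in low-weight septic neonates. If 1 mL is enough for the primary assay, up to 1.7 mL of each draw is not needed for it. No estimate, test or sample size depends on this point.

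**Working it through.** **Inputs from the article**
- Blood volume: about 240 mL at about 3 kg (Introduction), so 240 / 3 = 80 mL/kg.
- Volume per draw: 2.7 mL (5.6, 5.18). Maximum number of draws: 3 (5.10, 5.18).
- Stated need: 1 mL (Introduction).

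**Assumption.** The article gives no weight range, so weights below 3 kg are mine.

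**Plan's own figure.** The plan gives 3 draws of 2.7 mL but no total or percentage to reproduce. The count agrees between 5.10 and 5.18, and the volume agrees between 5.6 and 5.18. The total is 3 × 2.7 = 8.1 mL.

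**Share of blood volume** = (draws × volume) / (80 × weight)

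| Weight | Blood volume | Two draws of 2.7 mL | Three draws of 2.7 mL | Three draws of 1 mL |
|---|---|---|---|---|
| 3 kg (documented) | 240 mL | 5.4/240 = 2.25% | 8.1/240 = 3.4% | 3/240 = 1.25% |
| 2 kg (assumed) | 160 mL | 5.4/160 = 3.4% | 8.1/160 = 5.1% | 3/160 = 1.9% |
| 1.5 kg (assumed) | 120 mL | 5.4/120 = 4.5% | 8.1/120 = 6.75% | 3/120 = 2.5% |
| 1 kg (assumed) | 80 mL | 5.4/80 = 6.75% | 8.1/80 = 10.1% | 3/80 = 3.75% |

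At 1 kg, the gap between 2.7 mL and 1 mL over three draws is 3 × 1.7 = 5.1 mL, and 5.1/80 = 6.4% of blood volume.

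**Sensitivity to mL/kg.** If preterm blood volume is 90 to 100 mL/kg (assumption), three 2.7 mL draws at 1 kg take 8.1/90 = 9.0% to 8.1/100 = 8.1%.

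**A scaled draw built from the article's figures**
- Rate: 2.7 mL / 3 kg = 0.9 mL/kg. Three draws take 3 × 0.9 / 80 = 3.4%, whatever the weight.
- This gives 1.8 mL at 2 kg and 1.35 mL at 1.5 kg. It reaches 1 mL at 1 / 0.9 = 1.1 kg.
- With a 1 mL minimum, the 3.4% holds only from 3 kg down to 1.1 kg. Below that, three draws take 3/80 = 3.75% at 1 kg and 3/40 = 7.5% at 0.5 kg.
- To stay within 3.4% there, the number of 1 mL draws must not exceed 0.03375 × 80 × weight = 2.7 × weight. That allows two draws at 1 kg (2/80 = 2.5%) and one at 0.5 kg (1/40 = 2.5%).

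**The case against.** The strongest objection is that this is a condensed article. A full protocol (version 1.2), local operating procedures and an ethics approval exist, and a weight-based limit may well be in them. That is a fair caution, and the fix allows for it. It does not remove the point, because the article states a volume twice and leaves it unqualified; the issue is a rule that is given, not one left out.

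The size also needs care. At the only documented weight the maximum is 3.4%. The larger figures need assumed weights, and three draws is a conditional ceiling: the further sample needs a physician's indication, and Table 5 brackets the 72-hour sample. That stands, which is why two-draw figures are shown alongside.

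A reader might infer more than the documents support:

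- **That 1 mL and 2.7 mL contradict each other.** They may be an assay minimum and a research tube. Section 5.6 sets plasma aside "in order to later determine the concentration of the reactive metabolite methylglyoxal", and section 3 lists "Examination of the metabolome in plasma and urine to identify risk profiles" together with RNA and nucleosome aims. The article does not say that this is the reason, so the difference is unexplained and no contradiction is shown.
- **That 1 mL is proven sufficient in practice.** Section 5.6 states the input as a mass: "The so-called NGS libraries are made from 0.5 to 1 ng cfDNA". This does not tie NGS to 2.7 mL, but it does not show that 1 mL always yields enough after extraction and quality control either.
- **That the draws are unsafe, or the description of low blood loss is false.** Nothing in the article shows this at 3 kg, and it sets no threshold for lower weights.
- **That recording of draw-related events is optional.** Section 5.18 says only that such events can be entered in the eCRF. Section 5.14 makes investigators responsible for complete and correct eCRFs, and section 5.17 allows checks against source documents. The wording alone does not show that recording is left to choice.

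**Conclusion.** The point holds as a minor safety matter. Followed as written, sections 5.6 and 5.18 take the same 2.7 mL from a preterm neonate as from a toddler, and the Harms section does not consider volume. The three-draw maximum is 3.4% of blood volume at 3 kg. At an assumed 1 kg it is 10.1%, with 6.75% for two draws. These shares rest on the article's 80 mL/kg and on low weights that the article neither gives nor excludes. How much of the volume is avoidable rests on the article's own statement that 1 mL is enough.

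**What to change.** In sections 5.6 and 5.18, scale the NGS draw for neonates below 3 kg. One option is 0.9 mL/kg per draw, with a 1 mL minimum and a 2.7 mL maximum; draws at 3 kg and above stay as they are. State that NGS has first call on the plasma and that the methylglyoxal, metabolome, RNA and nucleosome assays use what remains. If the full protocol already sets a weight-based limit, state that limit instead.

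Below about 1.1 kg the 1 mL minimum governs, so the sponsor and the ethics committee should also limit the number of draws there. They should set the final figures.

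The change costs a few sentences. The downsides are less plasma for secondary assays in the smallest neonates and possibly some low-yield NGS samples if 1 mL proves too little in practice.
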